## Methods and analysis

### Adaptation of fencing activity

Considering the high technical component of foil and saber, two fencing specialties, an adapted form of fencing is proposed that allows participants to enjoy the training more. As it is a one-sided sport, participants are encouraged to change the grip of the weapon several times during training in order to use both limbs equally and not to neglect the operated side. To avoid possible complications, low weight foil and saber are used within the APA. The wide use of parries forces the fencer to make larger movements that allow greater involvement of the shoulder joint to improve the range of movement of the operated arm. The content was developed by the Università degli Studi di Roma Tor Vergata in collaboration with [name], specialist in sports medicine and Olympic foil champion; [name] and [name], foil, and saber coaches of Olympic fencers, respectively. From an athletic performance perspective, it must be considered a moderate-intensity physical activity (i.e., participants feel increased heart rate, respiration, and body temperature, but are still able to carry on a conversation), with the added benefit of being safe, psychologically engaging, fun, and social to encourage broad participation and minimal dropout (44).

### Design of FENICE trial

The FENICE study is a mono-center, randomized clinical trial targeting women with stages I-III BC within four weeks from surgery, conducted at the Breast Unit of Policlinico Tor Vergata Rome and Frascati Scherma ASD. The sequence of study and control group is randomized to minimize the influence of time-dependent variables. The participants, regardless of arm dominance, will be followed up by oncologists, radiotherapists, and surgeons according to the BC guidelines. All subjects participating in the study will undergo a sports medicine examination to objectify whether there are any alterations or diseases that pose a risk to the patient and to determine whether the patient needs to have additional tests and more specific examinations performed. For participants in the study arm only, APA consists of two fencing sessions (1 h/session) per week within 15 days of enrollment. The minimum number of sessions for the assessment of the primary endpoint is 48 sessions over six months up to a maximum of 96 sessions over 12 months (**Figure 2**).

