### Follow up visits

Participants will be included in the FENICE study for a total of 24 months and will be followed up differently based on the inclusion arm. In the study arm (APA and Mediterranean diet arm) patients will be monthly followed up for comorbidities, co-medication and herbal remedies, adverse events, and body mass index (BMI). Moreover, every three months also clinical evaluation, blood parameters, instrumental exams and QoL questionnaires will be carried out for the study arm patients. In the control arm, instead, all the mentioned parameters will be followed up every three months (see **Figure 2**).

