### Data collection

Participants will be included in the study and will undergo several follow-up visits. During the follow-up period trained research nurses/data managers will contact patients at baseline (T=0) (± one week), and subsequently every four weeks (± two weeks), to go through a standardized questionnaire and to collect data on the outcomes of sequelae and clinical symptoms/AEs. In addition, all patients will be contacted by the research nurse/data manager at the end of the APA period (± two weeks from the end) to complete a last questionnaire. Research nurses/data managers additionally will collect required laboratory and or test results from participants’ (electronic) medical records. If a subject discontinues the APA and lifestyle interventions during the 12-week follow-up period, follow-up will continue.

The questions within the surveys will be performed to assess the occurrence and severity of any new symptoms experienced by the participants, and the global physical and psychological health after the beginning of APA. The questionnaires that will be administered to participants during the study period are listed in **Table 4**.

**Table 4 T4:** Type of questionnaire that will be administered to breast cancer patients.

Objective	Questionnaire
**Disability**	The DASH (disabilities of the arm, shoulder, and hand measurement tool) questionnaire
**QoL**	EORTC qlq-C30 and EORTC qlq- BR23 questionnaire
**Fatigue**	The MFI 20 (Multidimensional fatigue inventory) questionnaire
**Anxiety-depression**	The HADS (Hospital anxiety and depression scale) questionnaire
**Physical activity and sedentary behavior**	The short version of the IPAQ (international physical activity questionnaire)
**Oedema assessment**	Disability scale for oedema

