### Sample size

The hypothesis guiding the formal determination of the sample size proposes an expected improvement of at least 15 points in the mean DASH score. The DASH score is a valuable, pragmatic, and frequently utilized metric in individuals with various musculoskeletal disorders of the upper limb. Ranging from 0 to 100, it encompasses responses to 30 questions (https://orthotoolkit.com/dash/) An improvement of at least 15 points is considered clinically significant in enhancing functional ability. The statistical parameters are configured in a highly conservative manner, considering the non-pharmacological nature of the intervention (adapted physical activity) and the inherent inter-individual variability in response, particularly within the treated group (Group 1). Therefore, with alpha and beta errors set at 0.01, a standard deviation in Group 1 that is twice that of Group 2 (SD: 20 compared to 10), even exceeding the hypothesized difference (15 points), 56 patients per group are deemed necessary. Considering the enrollment capabilities of our group and potential physiological withdrawal of patients, the sample size has been increased to 150 total patients. The target population will be at least 18 years of age (of any ethnicity) with a diagnosis of non-metastatic breast cancer and already treated with surgery for the primary tumor. This total will be divided into two sub-groups by randomization in blocks of 75 patients each (intervention group, Group 1, and control group, Group 2). The first group will be distinguished by subjects treated with adapted physical activity rehabilitation and with correct lifestyle suggestions. The second group, on the other hand, will be characterized by standard care without physical activity rehabilitation or lifestyle suggestions.

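### Read literally, the 48-session minimum makes primary endpoint assessment depend on 92–100% attendance in the APA arm only; the article should rule this reading out and fix one assessment time for both arms

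*Protocol article*

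**What the plan says.** Under *Design of FENICE trial*, the protocol article gives sessions to one arm: "For participants in the study arm only, APA consists of two fencing sessions (1 h/session) per week within 15 days of enrollment". The next sentence reads "The minimum number of sessions for the assessment of the primary endpoint is 48 sessions over six months" and continues "up to a maximum of 96 sessions over 12 months".

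Controls have nothing to attend. *Sample size* describes their care as "standard care without physical activity rehabilitation or lifestyle suggestions". Their assessments follow the calendar (*Follow up visits*): "In the control arm, instead, all the mentioned parameters will be followed up every three months".

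*Data collection* says what happens when a woman stops the intervention: "If a subject discontinues the APA and lifestyle interventions during the 12-week follow-up period, follow-up will continue". The same section has all patients contacted for a last questionnaire at the end of the APA period.

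The sample size is driven by "an expected improvement of at least 15 points in the mean DASH score". The primary objective is wider: overall physical and mental status, including adverse events.

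**The concern.** A minimum number of sessions is something that only the APA arm can fail. If it decides who is assessed, one arm is selected on a variable observed after randomisation while the other is kept whole, and the two groups compared are no longer those that randomisation made alike.

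Attendance here is plausibly prognostic. Women enter within four weeks of surgery and may have further oncological treatment planned. The article's own Table 1 links these treatments to fatigue, pain, lymphedema and restricted shoulder mobility. Women who miss sessions may therefore be those with worse arm function, which is what DASH measures. Leaving them out would make the APA arm look better than it is.

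The same sentence also leaves the time of assessment open between six and 12 months. A time defined by session count has no meaning for controls.

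**Working it through.** **1. How strict the minimum is, read literally.** Inputs from *Design of FENICE trial*: two sessions a week, 48 sessions, six months; 96 sessions, 12 months.
- Six months as 26 weeks: 2 × 26 = 52 sessions; 48/52 = 92.3%.
- Six months as 24 weeks (four-week months, and the 24 weeks of follow-up in the inclusion criteria): 2 × 24 = 48; 48/48 = 100%.
- Twelve months as 52 weeks: 2 × 52 = 104; 96/104 = 92.3%.

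**2. Whether another section overrides it.** The discontinuation sentence refers to a 12-week period, which holds 2 × 12 = 24 sessions, half of the 48. It keeps women under follow-up but does not say that their data enter the primary endpoint assessment. The end-of-APA questionnaire for all patients suggests that data will be collected whatever the attendance, but again does not link them to the primary endpoint. The two sections can be made compatible, but the article does not do so.

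**3. Reproducing the plan's sample size.** Inputs from *Sample size*: difference 15, SDs 20 and 10, alpha and beta 0.01.
- Normal approximation, two-sided: n = (20² + 10²) × (2.576 + 2.326)² / 15² = 53.4, so 54 per group.
- Two-sided Welch t: power 0.9891 at n = 55 and 0.9904 at n = 56, so 56 per group, as stated.

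The figure of 56 is not in dispute.

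**4. Size of the bias if the rule were applied.** Shift in the APA mean = fraction excluded × (mean DASH of excluded − mean DASH of retained). Both inputs are assumptions; the documents give neither.
- 20% excluded, 5 points worse: 0.2 × 5 = 1 point (1/15 = 7% of the target difference).
- 40% excluded, 15 points worse: 0.4 × 15 = 6 points (6/15 = 40%).
- No difference between excluded and retained: 0 points.

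A simulation gives the same picture. It assumes no treatment effect, 75 per arm, retention of the best APA attenders, all controls kept, and a two-sided 5% test. The correlation is between attendance and better DASH.

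| APA SD / control SD | Correlation | Share of APA arm retained | Spurious benefit (points) | Type I error |
|---|---|---|---|---|
| 20 / 10 | 0 | 30–70% | about 0 | about 5% |
| 20 / 10 | 0.3 | 70% | 3.0 | 17% |
| 20 / 10 | 0.3 | 50% | 4.6 | 27% |
| 20 / 10 | 0.3 | 30% | 6.9 | 36% |
| 10 / 10 | 0.3 | 70% | 1.5 | 13% |
| 10 / 10 | 0.3 | 50% | 2.3 | 22% |
| 10 / 10 | 0.3 | 30% | 3.4 | 30% |

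The 10/10 rows are included because the plan attributes the larger SD to varying response to the intervention, which need not appear if there is no effect.

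**5. Whether numbers are the problem.** Each arm has room for 75 − 56 = 19 losses (25.3%). Falling below 56 costs little, because 56 was set for 99% power at alpha 0.01. With, say, 40 APA women against 75 controls, SE = √(400/40 + 100/75) = 3.37 and 15/3.37 = 4.46. Power is then Φ(4.46 − 2.576) = 97% at two-sided 0.01 and Φ(4.46 − 1.96) = 99% at 0.05. The issue is bias, not power.

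**6. Whether assessing everyone is affordable.** With 75 per arm, SE = √(500/75) = 2.58. The diluted effects are assumptions.

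| True mean difference | Power, alpha 0.01 | Power, alpha 0.05 |
|---|---|---|
| 15 (no dilution) | 99.9% | >99.9% |
| 10.5 (70%) | 93% | 98% |
| 7.5 (50%) | 63% | 83% |

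**The case against.** The best defence is that the sentence describes programme length, not a per-patient filter. At two sessions a week and four weeks a month, 48 and 96 are exactly the full six-month and 12-month schedules, and 48 sessions fit the 24 weeks of follow-up required at entry. A literal filter on that calendar would demand perfect attendance, which is unlikely to be intended in a programme that offers rest breaks and easier alternatives. Continued follow-up of discontinuers points the same way. This reading is plausible and may well be what was meant. It does not settle the matter, because the text ties a minimum number of sessions to the assessment of the primary endpoint.

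A reader might infer that the plan drops low attenders and compares the rest with all controls, so that randomisation is already broken. The documents do not support this. No section states such an exclusion or defines an attendance-based analysis set. The article's silence on analysis populations proves nothing either, since that is commonly left to the full protocol or the SAP. A reader might also infer that the trial would become underpowered; step 5 shows that this is largely not so.

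Two further limits stand. DASH drives the sample size but is not named as the primary endpoint, so stating the bias in DASH points is itself an inference. And every bias figure rests on assumed attendance and an assumed link with outcome.

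**Conclusion.** The point holds conditionally. The article states a session minimum for assessing the primary endpoint. Read literally, it imposes 92–100% attendance after randomisation on the APA arm alone, and nothing in the article excludes that reading or reconciles it with continued follow-up of discontinuers. If the rule is followed as written and attendance is related to arm function, the comparison is biased towards APA. The amount is unknown from the documents: illustratively 1–6 DASH points against a 15-point target, and nothing if attendance and outcome are unrelated. If the sentence only describes planned exposure, there is no bias, but the wording should say so. On either reading, the time of primary assessment is left open between six and 12 months and has to be defined in a way that applies to both arms.

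**What to change.** Reconcile *Design of FENICE trial* with *Data collection* by replacing the session-minimum sentence with wording such as:

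*The primary endpoint is assessed at one fixed time from randomisation, [time to be stated], the same in both arms, in all randomised women, who are analysed in the arm assigned whatever the number of sessions attended. The 48 sessions over six months describe planned exposure and define only a supportive adherence analysis.*

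The discontinuation sentence in *Data collection* should then say that follow-up continues to that time point and that the data enter the primary analysis. The investigators choose the time point, and the session schedule itself is not altered.

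The cost is wording, plus the effort of obtaining the assessment from women who attend little. The estimated effect may be somewhat smaller because non-attenders count. Step 6 shows that the planned 150 women can absorb moderate dilution; power suffers materially only if the effect falls to about half the target.

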**Figure 2 f2:**
[figure not shown]
Study design of the mono center randomized FENICE clinical trial. All screened patients will receive a complete clinical, psychological, and instrumental evaluation, (lifestyle, comorbidities, oncological treatments and their related sequelae and AEs). Participants in the control arm will receive the usual recommendations based on the good clinical practice guidelines and according to 1) the stage of BC disease; 2) planned oncological treatments; 3) sequelae and AEs caused by oncological treatments. In the study arm, participants will be treated with the usual clinical and therapeutic recommendations together with APA and correct lifestyle suggestions (Mediterranean diet). All participants will be followed up for a minimum of 12 month, and up to a maximum of 24 months.

After a warm-up period dedicated to muscle awakening and progressive cardio-respiratory stress, participants begin specific fencing exercises, starting with basic footwork (advance, retreat, lunge) and ending with actions in which the injured side holds the saber. During the main activity (40 minutes of fencing), exercise intensity will be individually tailored based on a preliminary assessment. All participants will undergo an exercise stress test on a cycle ergometer during the recruitment phase of the study. This test will measure key physiological parameters, including heart rate, oxygen consumption (V’O2), and the MET (Metabolic Equivalent of Task) values achieved (45). The MET value, which represents the energy cost of physical activities, will be used to calibrate the intensity of physical exertion during training sessions. Specifically, the fencing exercises will be designed to reach an intensity that is approximately 60-70% of the participants’ maximal MET values determined during the stress test. This range corresponds to moderate-intensity exercise, which has been shown to be effective in improving cardiovascular fitness and overall health. Additionally, to ensure safety and maximize adherence, participants’ heart rates will be monitored during training to maintain the desired intensity. The target heart rate zone will be calculated using the Karvonen formula, which considers the participants’ resting heart rates and the intensity percentage derived from their stress test results. This individualized approach ensures that participants engage at a cardio-respiratory intensity that is challenging yet enjoyable. They will be encouraged to maintain a level of exertion where they can still respond verbally (the “talk test”), indicating they are working within a safe and effective moderate-intensity zone (46–48).

Adapted fencing includes offensive and defensive actions, which are performed considering the mobility of the shoulder. The primary (tierce = outside; quart = inside; fifth = head) and secondary blocks are therefore performed by patients with maximum mobility, without ever causing pain. Coordination, agility, and strength are encouraged during exercises between patients and during lessons with the fencing master. The adapted fencing lesson ends with a cool-down period. Since different subjects experience different physical outcomes for the cancer and the subsequent treatment, the program must address these individual needs while respecting safety principles. Therefore, rest and water breaks will be provided when necessary, and simplified or less strenuous movements will be suggested as alternatives for those who find parts of the workout too challenging or unsafe. In addition, participants are encouraged to use both saber and foil, also depending on which master is holding the training session. In any case, the weapons used will be adapted in material to avoid excessive strain or fatigue as stated above. Moreover, the courses and masters allow 12 participants per session with a maximum ratio of 1 master per 2.5 participants. During the study protocol, participants are also encouraged to follow healthy diet and adhere to the standards of the Mediterranean diet through the prescription of a personalized diet by a nutritional biologist involved in the project. Conventional bioelectrical impedance (BIA) testing to assess body composition is also planned during protocol follow-ups. To assess adherence to the Mediterranean diet, the Prevención con Dieta Mediterránea (PREDIMED) questionnaire will be completed both at the beginning and at the end of the study (49). The participants of the FENICE study will be followed up by several specialists before and during the APA period (**Figure 3**). This study was approved by the ethic board of the Policlinico Tor Vergata of Univeristy of Rome and the enrollment will start in September 2024 and the recruitment will take an 18 months’ time window for the inclusion of the expected 150 participants.

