## Introduction

Breast cancer (BC) is a growing global public health concern. Over time, different risk factors have been identified: alongside the genetic mutations (most commonly involving BRCA1 and BRCA2) implicated in hereditary form of breast and ovarian cancer, the most important risk factors for the sporadic form include personal and family history of BC, wide fertile window (related to early menarche, older age at menopause, first pregnancy after the age of 30 and nulliparity), the exposure to external sources of hormones (during hormone replacement therapy or using oral contraceptives), dense breast tissue and lifestyle based risk factors as alcohol consumption, tobacco, physical inactivity and sedentary lifestyle (1–4). The cancer screening programs in Italy comply with the guidelines established at European level, which are contained in the EU recommendation of December 16, 2003. These guidelines identify the three screening programs (breast, uterine and colorectal cancer) as the most effective cancer prevention measures (5). Despite the national cancer screening program launched since 2005, BC still affects many women in Italy. According to the latest AIRTUM (Associazione Italiana Registri Tumori) report, almost 56,000 new cases of BC have been diagnosed in our country in 2023, representing 30% of female tumors and 13% of all tumors regardless of gender (6, 7). At the same time the survival rate of patients has significantly improved (88% of 5-year survival rate) due to the recent treatments progress and the number of cancer survivors raised from approximately 2 million in 2006 to 3.6 million in 2020 (AIRTUM – Associazione Italiana Registri Tumori) (7). Improving prognosis due to early diagnosis and advances in therapeutic treatments has drawn the attention of health care professionals on disease related long-term side effects and on the multiple treatments BC patients must undergo (8). However, surgery represents the standard treatment for loco-regional BC, while radiotherapy (RT), antiblastic chemotherapy (AC), target therapy, immunotherapy and endocrine treatment are used in adjuvant and metastatic BC settings. During the past decades, conservative surgery (quadrantectomy) has become the first choice whenever possible, limiting mastectomy in selected cases only. Despite advances in procedures, surgery still has multiple detrimental effects, including pain, edema, and limited mobility (9–11). Posture very often appears to be compromised after mastectomy because the surgical scar limits arm mobility (e.g., internal rotation and shoulder droop are common, typically causing back pain) (12). In addition, the removal of lymph nodes (both the sentinel procedure and axillary lymph node dissection) is cited as a common cause of limited mobility and postoperative pain. Moreover, cancer treatments are also responsible of numerous long-term side effects as specified in **Table 1** (8, 13–18). Particularly, the use of aromatase inhibitors has been associated with possible risk of arthralgia and bone health worsening (19, 20). These aspects negatively affect the health-related Quality of Life (QoL) of BC patients (21, 22). BC patients also reported low levels of Work Ability (WA) and reduced outcomes in terms of employments status, employability, and fitness for work (23, 24). Some randomized clinical trials (25, 26) have demonstrated the benefit of regular and appropriate Adapted Physical Activity (APA) during and after BC treatment, particularly in terms of improved health status, strength, QoL and physical function, and fatigue reduction (**Table 2**) (35, 36). Moreover, two meta-analysis highlighted an inverse relationship between post-diagnosis APA and cancer-related mortality in patients with breast cancer compared to patients practicing low or no physical activity (37, 38). From another study emerged that patients with ER/PR negative cancer who had been physically active before the diagnosis had a significantly reduced risk for breast cancer recurrence compared to physically inactive patients (39). In early BC and in metastatic BC setting has been recently demonstrated that physical activity integration is able to improve general and physical well-being and mental health (40). Accordingly, these non-pharmacological treatments that alleviate long term side effects should be rated as a public health priority, as their role is crucial in improving overall survival (OS) and QoL in BC, cancer survivors included. For this reason, fostering APA and healthy lifestyle (including a balanced Mediterranean diet and weight management) should become an everyday purpose of healthcare professionals (41). In this context, APA as fencing has proven its affinity and efficacy as a supportive activity both during and after the treatment of BC patients (30, 35, 42, 43).

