
**Table 1 T1:** Side effects related to cancer treatments in breast cancer patients.

Late Side effects	Type of treatments				
	Chemotherapy	Endocrine therapy	Radiotherapy	Surgery	Target Therapy
**Arthralgia**	✗	✓✓✓	✗	✗	✗
**Bone health**	✓	✓✓✓	✓	✗	✗
**Cardiovascular disease**	✓✓	✗	✓	✗	✓✓✓
**Depression and anxiety**	✓✓✓	✓	✓✓	✓	✓✓
**Fatigue**	✓✓✓	✓	✓✓	✗	✓✓
**Lymphedema**	✗	✗	✓	✓✓	✗
**Metabolic disturbances**	✓	✓✓	✗	✗	✓
**Neurocognitive dysfunction**	✓	✗	✓	✗	✓
**Pain**	✓	✗	✓✓	✓✓✓	✗
**Peripheral neuropathy**	✓✓✓	✗	✗	✓	✗
**Respiratory impairment**	✓	✗	✓✓	✗	✓
**Sexual disfunction**	✓	✓✓	✗	✗	✗
**Shoulder limited mobility**	✗	✗	✓	✓✓	✗

✓✓✓Probably related (data from RCTs); ✓✓Might be related (data from RCTs with smaller samples); ✓Could be related (single-arm studies); ✗No sufficient data.

**Table 2 T2:** Beneficial effects of Adapted Physical Activity in cancer patients.

Sport/physical activity	Benefit	Reference
**Aerobic training**	**↓**CRF, **↑**health related QoL and physical function, **↓**anxiety, depression, **↑**sleep quality.	(27)
**Cycling**	**↑**QoL, **↑**Physical functioning, **↑**general health, **↑**vitality.	(28)
**Dragon Boat**	↑QoL, ↑Physical functioning, ↓fatigue.	(29)
**Fencing**	**↑**immunity function, **↑**adherence to therapies, **↑**health related QoL, **↓**CRF, **↓**anxiety, **↑**of the functional capacities.	(30)
**Resistance training**	**↓**CRF levels, **↑**health related QoL and physical function, **↓**lymphedema, **↑**aspects related to bone health.	(31)
**Rowing**	**↑**upper extremity and hip range of motion, **↑**lower and upper extremity strength, **↑**aerobic capacity and heart rate at rest and after prolonged effort.	(32)
**Swimming**	**↑**Flexion and external rotation of the operated arm.	(33)
**Walking**	**↓**Of the BMI, **↓**breast symptoms and in the arms, **↑**MS at the extremity of the upper limbs, **↓**of pain.	(31)
**Yoga**	**↑**joint mobility, **↑**muscle strength, **↑**QoL.	(34)

↓reduce; ↑ improve; CRF, cancer related fatigue; QoL, quality of life; BMI, Body mass index; MS, Muscle Strength.

Fencing can be a good activity to reduce fatigue, pain and limited arm mobility. As it is also a sport that naturally strengthens willpower, practicing fencing can have a positive effect on the attitude and psychological state of participants. Hence, the FENICE study protocol here described will assesses both physical and psychological outcomes.

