### Statistical analysis

The descriptive statistical analyses, the central tendency, variability, symmetry and kurtosis will be calculated, all accompanied by appropriate graphical representations. Regarding the inferential analyses, we will continue with the verification of the parametric and non-parametric hypotheses, respectively for the quantitative variables with parametric tests such as: Student’s t-test, Fisher’s F-test, etc. and for categorical variables using non-parametric tests such as: chi-square, Mann Wittney’s U, Fisher’s exact test, etc. Only results with p-values ≤ 0.05 will be considered statistically significant. Principal component analysis (PCA) will be adopted to explore the relationships among secondary variables and identify patterns of improvement related to the APA intervention (50).

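### The named tests make no use of planned adjuvant treatment, so the AE, fatigue, mood and bone comparisons give up a modest amount of precision and leave chance imbalance uncorrected

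*Protocol article*

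**What the plan says.** **Baseline information.** The Figure 2 legend says that all screened patients are evaluated for, among other things, their oncological treatments and the consequences of these. In the control arm, usual recommendations are given "according to 1) the stage of BC disease; 2) planned oncological treatments; 3) sequelae and AEs caused by oncological treatments". The treatment plan is therefore known when a woman enters the trial.

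**Link to outcomes.** The Introduction states that "the use of aromatase inhibitors has been associated with possible risk of arthralgia and bone health worsening" and refers to Table 1 for the wider list. Table 1 grades each treatment-effect pair; the top grade in its footnote begins "Probably related (data from RCTs". Chemotherapy has that grade for fatigue and for depression and anxiety, and endocrine therapy for bone health.

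**Outcomes concerned.** The number and severity of adverse events (AEs) belong to the primary objective. Fatigue, bone health and lipids are in the secondary objective. Mood is measured by HADS (Table 4).

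**Allocation and analysis.** The Sample size section randomises 75 women to each arm and names no stratification factor. The Statistical analysis section tests hypotheses "respectively for the quantitative variables with parametric tests such as" Student's t and Fisher's F, and categorical variables with chi-square, Mann-Whitney and Fisher's exact tests. Both lists are left open. Principal component analysis is added to explore the secondary variables; it does not adjust the contrast between arms.

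**The concern.** Women enter within four weeks of surgery and train for six to twelve months, a period in which adjuvant treatment would usually be given. Some will have chemotherapy, radiotherapy or endocrine therapy and others will not, and the document expects these treatments to affect several of the outcomes being compared.

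A baseline factor that predicts the outcome can be used in two ways: balanced at allocation or included in the analysis model. The text names neither. Two things follow. Outcome variation due to planned treatment stays in the error term, so intervals are wider than they need be. And if, say, more women with planned chemotherapy fall in one arm, the estimate moves and nothing corrects it. If no model is fixed in advance, such an imbalance also invites a choice between adjusted and unadjusted results after the data are seen.

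**Working it through.** **1. The plan's own figure.** Inputs from the Sample size section: "an expected improvement of at least 15 points in the mean DASH score", SDs of 20 and 10, and "with alpha and beta errors set at 0.01". Taking the test as two-sided (the text does not say), the normal formula is

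n = (2.576 + 2.326)² × (20² + 10²) / 15² = 53.4, so 54 per group.

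The noncentral t calculation gives 56 (power 0.9904 with Welch degrees of freedom; 0.9891 at 55). The statement "56 patients per group are deemed necessary" is reproduced. It concerns DASH only and is unaffected by this point.

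**2. What Table 1 supports** (3 ticks = top grade, 0 = insufficient data):

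| Outcome row | Chemo | Endocrine | Radio | Surgery | Target |
|---|---|---|---|---|---|
| Fatigue | 3 | 1 | 2 | 0 | 2 |
| Depression and anxiety | 3 | 1 | 2 | 1 | 2 |
| Bone health | 1 | 3 | 1 | 0 | 0 |
| Metabolic disturbances | 1 | 2 | 0 | 0 | 1 |

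Fatigue, mood and bone health each have a top-grade link. Lipids have no row of their own; the nearest, metabolic disturbances, reaches the middle grade at most.

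**3. Chance imbalance.** Assumption: 30-50% of women have planned chemotherapy, with unstratified 75:75 allocation. The SD of the difference in proportions is √[2p(1−p)/75], which is 7.5 points at p = 0.3 and 8.2 points at p = 0.5. Exact probabilities from two independent binomials:

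| Per arm | p | Difference ≥ 10 points | Difference ≥ 15 points |
|---|---|---|---|
| 75 | 0.3 | 18% | 4% |
| 75 | 0.5 | 22% | 6% |
| 56 | 0.3 | 26% | 8% |
| 56 | 0.5 | 30% | 11% |

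**4. What an imbalance does.** For a continuous outcome that treatment shifts by d SD, a 10-point imbalance moves the unadjusted difference by 0.10 × d, which is 0.03 to 0.08 SD for d = 0.3 to 0.8. The standard error of the difference is √(2/75) = 0.163 SD, so the move is about 0.2 to 0.5 standard errors.

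For AE counts, if chemotherapy multiplies the rate by RR and the arms differ by δ, the ratio due to imbalance alone is [1 + (p + δ/2)(RR − 1)] / [1 + (p − δ/2)(RR − 1)]. With δ = 0.10:
- p = 0.5, RR = 1.5: 1.275 / 1.225 = 1.04
- p = 0.3, RR = 3: 1.70 / 1.50 = 1.13

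**5. Precision forgone.** For one binary factor, R² = p(1−p)d² / [1 + p(1−p)d²], and adjustment multiplies the standard error by √(1 − R²).

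| d (SD) | R², p = 0.3 to 0.5 | Cut in standard error |
|---|---|---|
| 0.3 | 1.9-2.2% | about 1% |
| 0.5 | 5.0-5.9% | about 3% |
| 0.8 | 11.8-13.8% | 6-7% |

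**6. Power.** For a true effect of 0.4 SD, 75 per arm and two-sided 0.05 (normal approximation), power is 68.8% unadjusted, 71.0% at R² = 5% and 73.3% at R² = 10%.

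**The case against.** The strongest case against is that this is analysis-plan content. The article is condensed, no analysis plan is shown, both test lists are open, and nothing rules out covariates. That stands to this extent: the document does not say that planned treatment will be ignored, and a fuller plan may already adjust for it. It does not dispose of the point, because the section does state a method, and every between-arm test in it is of a kind that cannot use this information.

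Three stronger readings are tempting, and the document does not support them:

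- *The unadjusted comparisons are biased.* They are not. Under randomisation their type I error and standard error already allow for chance imbalance.
- *The document names treatment as the cause of these outcomes.* The phrase about AEs caused by treatment describes what usual care is tailored to, not the trial's AE outcome. Table 1 grades associations, the Introduction speaks only of a possible risk with aromatase inhibitors, and the lipid link is weak.
- *The gain would be large.* For chemotherapy alone to explain 30% of outcome variance at 30-50% prevalence, it would have to shift the outcome by about 1.3-1.4 SD (√(0.4286/0.25) to √(0.4286/0.21)). Nothing in the document points to that.

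Two further reservations stand. The legend records oncological treatments in all screened women, but the word planned appears only for the control arm, so a planned-treatment field in both arms is an inference. And the precision argument carries over directly only to continuous outcomes: adjusting an odds ratio for a binary AE changes what is estimated.

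**Conclusion.** The point holds as a recommendation to prespecify adjustment, not as a demonstrated error. The named between-arm tests do not use a baseline factor that the document itself links to fatigue, mood, bone health and AEs. They remain valid, but they forgo some precision and leave chance imbalance uncorrected.

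The size is small to moderate: an 18-22% chance of a chemotherapy imbalance of 10 or more points, a standard error about 1-7% larger than necessary, and two to four points of power for a 0.4 SD effect (R² of 5-10%). All of this rests on assumed prevalence (30-50%) and an assumed treatment effect on the outcome (0.3-0.8 SD), since the document gives neither. The DASH sample size is untouched.

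**What to change.** State in the Statistical analysis section that:

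- between-arm comparisons of fatigue, mood and bone health use linear models, and AE counts use a count model reporting a rate ratio, which avoids the change of estimand that comes with an adjusted odds ratio;
- each model contains arm plus a short prespecified set of planned-treatment indicators: at least chemotherapy yes/no, with radiotherapy and endocrine therapy where relevant to the outcome;
- the indicators are treatment as planned and recorded before randomisation in both arms, not as later received, because the arm may influence the latter;
- the unadjusted comparison is kept as a sensitivity analysis.

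If a fuller plan already does this, one sentence in the section settles the matter. The cost is a few lines of text, a few model terms, and a check that planned treatment is recorded at baseline for both arms. No extra patients or visits are needed.
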